## Abstract

**Background:**

With population-wide vaccination availability, the global COVID-19 pandemic entered a new phase. Despite vaccination status, some people who were infected with SARS-CoV-2 experience long-term symptoms.

**Objective:**

In this study, we aim to characterize the long-term effects of SARS-CoV-2 infection and the pandemic. We also aim to build symptom clusters and determine risk factors for developing long COVID symptoms. Furthermore, we assess social participation and health-related quality of life in patients with long COVID and in the general population during a global pandemic.

**Methods:**

With a mixed-methods, web-based approach, we aim to recruit 2000 people in Germany who are older than 18 years and can provide informed consent. In the quantitative arm of the study, we identify symptoms of and predictive factors for long COVID manifestations with cluster analysis and assess social participation during the pandemic with standardized questionnaires. The qualitative arm of the study uses individual interviews and focus group discussions to better understand the illness experience of persons who experience long COVID.

**Results:**

Recruitment started in September 2021. Up until July 2022, we recruited approximately 4500 participants via our web-based database.

**Conclusions:**

This study aims to build an innovative, patient-centered, web-based research platform appropriate for the pandemic by minimizing physical contact between study personnel and participants. All study activities are designed to better understand the long COVID syndrome, social participation during the pandemic, and the illness experiences of persons affected by long COVID.

**Trial Registration:**

German Clinical Trial Registry DRKS00026007; https://tinyurl.com/yh282fkt

**International Registered Report Identifier (IRRID):**

DERR1-10.2196/38718

## Introduction

### Overview

In the beginning of the SARS-CoV-2 pandemic, lockdown and restrictions were the main measures to control further transmission of the virus. In 2021, we entered a new era of the pandemic, with several effective vaccines. Politics, society, and science developed and established effective measures for the control of the transmission of the virus. Nevertheless, more than 320 million people were infected worldwide until now, and more than 5 million people died because of the infection [1]. Approximately 10% of the infected people report symptoms 4 to 12 weeks after the COVID-19 infection, now called “Long COVID” or “Post COVID“ syndrome (hereafter: long COVID [2]). The symptoms after a SARS-CoV-2 infection are various; a study from the United Kingdom reported 55 different long-term effects [3]. In the German guideline, different symptoms of long COVID are described, such as headache, shortness of breath, cough, dysosmia or anosmia, cognitive impairment or brain fog, and fatigue [4]. Patients report a great impact on their quality of life and ability to work or even to manage their everyday life [5]. The first steps in distinguishing predictors for some long COVID symptoms were made [6]. However, it remains unclear which patients are at higher risk for a prolonged course of the disease and if there are diagnostic tools to objectify long COVID.

Even with effective and available vaccines in Germany [7], it will take effort for individuals and society to find their way back to a *normal* everyday life. An important aspect of everyday life, which was dramatically altered during phases of COVID-19 pandemic lockdown, was social participation. Studies have shown that social participation is associated with life satisfaction, self-esteem, and mental health, for example, in older persons [8] and adolescents [9]. Therefore, understanding how people directly and indirectly affected by COVID-19 resume social participation in the vaccine era is also relevant for understanding the pandemic’s effect upon community health. The assessment of social participation during the pandemic and the active involvement of those affected by long COVID in research endeavors may provide important information on how measures, communication, and care services can be optimized in the future to best suit the health needs of the community.

### Primary Aim

With the joint project, DEFEAT Corona (Defense Against COVID-19 Study), we aim to improve the understanding of the long COVID syndrome and the long-term effects of the pandemic in a large cohort. We want to analyze which syndromic forms exist in patients with long COVID and how care structures should be built to ensure patient-centered support. We will assess how patients with long COVID participate socially in comparison to others who are also experiencing the pandemic.

With this study, we aim to build an innovative, web-based, and patient-centered research infrastructure to support the new challenges of the vaccine era of the COVID-19 pandemic.

## Methods

### Aim, Design, and Setting of the Study

The main goal of the joint project, DEFEAT Corona, is to create an innovative, web-based, and patient-centered research structure. With this platform, we want to face the challenges of the vaccine area in Lower Saxony, Germany. The 3 partners (Hannover Medical School, University Medical Center Göttingen, and Ostfalia University of Applied Sciences) plan to build a digital platform for long-term research in times of a global pandemic. There are 3 subprojects, which have the following primary and secondary objectives. Key to the project is to assess the long-term consequences of a SARS-CoV-2 infection and the pandemic in a prospective cohort study. This will be addressed in the 3 subprojects (Textbox 1).

Primary and secondary aims of DEFEAT Corona (Defense Against COVID-19 Study).
**Subproject 1: Back to life? Social and participation convalescence in the vaccine era**
Analysis of how social participation is experienced by patients who had COVID-19 and have long term symptoms (patients with long COVID) vs persons who were affected by pandemic regulations but not infected by the virusFoundation of a patient- and public-led advisory board
**Subproject 2: COVID-19 special consultation Lower Saxony—vaccination response and long COVID syndrome**
Establishment of a web-based, multimodal research platform and development of a self-assessment for patients with long COVIDSetup of an innovative and transregional special consultation service for patients with long COVID syndrome (clinical care and research)Finding objective measures for the diagnosis of long COVID (eg, optical coherence tomography angiography imaging and ear, nose, and throat examination)Assessment of the needs of patients with long COVID in health care
**Subproject 3: machine learning for finding symptom clusters (MACLEAF SYCL)**
Data preparation for exploratory analysis and definition of criteria for cluster analysisImplementation of the cluster analysis to identify symptom clusters with possible adjustments or extensions
**Overriding secondary objectives**
A transparent communication of new insights to a nonprofessional audienceSustainable transfer of knowledgeMaking research participation accessible for parts of the population living further away from university cities.

### Characteristics of the Participants

Participants will be recruited via newspaper announcements, home page, posters, and flyers in local regions, general practices, or long COVID support groups in the northern German region of Lower Saxony. Furthermore, participants will be recruited in the outpatient clinics of the Hannover Medical School and University Medical Center Göttingen, through the cooperation partners, local public health authorities, primary care clinics, and ministries.

Everyone older than 18 years who can give informed consent is invited to participate in the first baseline web-based questionnaire, whether they had COVID-19 (with or without long-term effects) or not. We will also assess whether the participants live in Lower Saxony. Exclusion criteria are being younger than 18 years and refusal or inability to provide consent. Participants for subproject 2 will be recruited from the participants of the baseline questionnaire. Subproject 3 will analyze data assessed in the baseline questionnaire.

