#### Step 1: Baseline Questionnaire

The baseline questionnaire will include sociodemographic questions, questions about a SARS-CoV-2 infection, the process of the disease, possible late symptoms, and vaccination status. According to the participants’ answers in the basic questionnaire, they will be assigned into 3 groups: “No COVID,” “Ex-COVID,” and “Long COVID.” Questionnaire items were adapted from the World Health Organization Case Report Form [10] and the UK Long COVID guideline [11]. We also assessed quality of life (EQ-5D [12]) and social participation (IMET [13]; Multimedia Appendix 1).

The data of the baseline questionnaire will also be used in the cluster analysis to characterize the typical symptom complexes experienced by participants with long COVID.

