#### Step 4: Individualized, Modular, Follow-up Questionnaires

All participants will get invitations for modular questionnaires, depending on their answer in the baseline questionnaire (eg, how their children experienced the pandemic, if the participants stated that they had children). The follow-up questionnaires will contain questions about new infections with SARS-CoV-2, changes in symptoms and recovery from symptoms, further vaccinations, quality of life (EQ-5D), and social participation (IMET) over a longer period. The project will be accompanied by a patient- and public-led advisory board.

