## Results

The study began in July 2021 with the preparation of the first questionnaire. The first participants were recruited in September 2021 via web-based questionnaire. Until July 2022, approximately 4500 participants were recruited via a web-based questionnaire. Recruiting will continue at least until the end of 2022. The first clinical consultations of patients with long COVID took place in January 2022 and will continue throughout the duration of the study.

The qualitative study began in September 2021 with a series of preliminary exploratory discussions with members of the target population to assess important subjects and develop an interview guideline. This guideline will be used in the main qualitative study. Interviews will be conducted and analyzed, and new participants will be enrolled according to the principle of theoretical sampling. The interviews started in January 2022 and will continue until targeted sample size is achieved.

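### The symptom clusters are stated to come from a baseline questionnaire answered at any time since infection; if symptoms drift, stages of one illness could appear as separate forms.

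*Protocol article*

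**What the plan says.** Primary Aim sets the question: "We want to analyze which syndromic forms exist in patients with long COVID". Two places name the data for answering it. Under Characteristics of the Participants: "Subproject 3 will analyze data assessed in the baseline questionnaire". Step 1 says that the baseline data will be "used in the cluster analysis to characterize the typical symptom complexes experienced by participants with long COVID".

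Entry is open to adults who consent, "whether they had COVID-19 (with or without long-term effects) or not". The only bars are these: "Exclusion criteria are being younger than 18 years and refusal or inability to provide consent". No minimum or maximum time since infection is set. On timing, Results states: "The first participants were recruited in September 2021 via web-based questionnaire". Recruitment is to go on at least until the end of 2022.

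Repeated symptom data are planned as well. The Step 4 questionnaires cover new infections and "changes in symptoms and recovery from symptoms, further vaccinations, quality of life (EQ-5D), and social participation (IMET) over a longer period". No section assigns these data to the cluster analysis.

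**The concern.** A baseline form answered on entry catches each person at one point of their illness, and that point differs between people. If some symptoms fade with time and others become more common, symptoms typical of the same phase will occur together across respondents even when everyone has the same illness. A clustering method sees only the co-occurrence and cannot tell phase from type. Baseline data alone may then show an early and a late cluster through which the same patient passes. Describing these as two syndromic forms would be a mistake on one of the project's stated aims. The follow-up data that could expose it are planned but not linked to this analysis.

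**Working it through.** The article gives no figure on this point, so there is none to reproduce. The check has two parts: what the text fixes, and how large the effect could be under stated assumptions.

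**From the article**
- Cluster input: the baseline questionnaire (Characteristics of the Participants; Step 1).
- Window for time since infection: none (Characteristics of the Participants).
- Entry period: September 2021 to at least December 2022, so 4 + 12 = 16 calendar months or more (Results).
- Sample: target 2000 over all three groups (Abstract); about 4500 recruited by July 2022, with no split by group (Results).
- Not given: time since infection, symptom frequencies, symptom trends, number with long COVID.

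**Mechanism**

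Suppose there is one illness and symptoms i and j are independent at any given time t since infection. Pooled over t, Cov(Xi, Xj) = Cov(pi(t), pj(t)). With t uniform and each probability changing linearly by Δ over the range, this equals ΔiΔj/12.
- Strong drift (assumed 70% to 10%): 0.6 × 0.6/12 = 0.030. Mean 0.40, variance 0.24, so the correlation is 0.030/0.24 = 0.125.
- Mild drift (assumed 60% to 20%): 0.4 × 0.4/12 = 0.0133; correlation 0.0133/0.24 = 0.056.
- Modest decline (assumed 60% to 35%): 0.25 × 0.25/12 = 0.0052; variance 0.475 × 0.525 = 0.249; correlation 0.021.

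Within one of three equal time bands each Δ is a third as large, so the covariance is a ninth as large.

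**Simulation A** (all inputs assumed): 10 binary symptoms, time uniform over 1 to 18 months, no true subtypes, latent class analysis with the number of classes chosen by BIC. Five symptoms fall and five rise, except where stated. Entries are runs with false classes.

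| Drift | Pooled, n = 1500 | Pooled, n = 500 | Three bands, 1500 people each |
|---|---|---|---|
| Strong (70% to 10%; 20% to 60%) | 20/20 | 20/20 | 0/60 |
| Mild (60% to 20%; 30% to 50%) | 8 to 12 of 20 in four sets of 20 runs | 0/20 | 0/60 |
| All ten decline, 60% to 35% | 0/20 | – | – |
| None | 0/20 | – | 0/60 |

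A second class adds 11 parameters, so BIC requires 2 × log-likelihood to rise by more than 11 × ln(500) = 68.4 at n = 500, or 11 × ln(1500) = 80.4 at n = 1500. The rise itself grows roughly in proportion to n. That is why mild drift shows up only in the larger sample. The bands of 1500 answer a natural doubt: with the sample size per analysis held at 1500, the false classes vanish once the time range is narrow, so the mixture of times produces them.

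**Simulation B** (all inputs assumed): 12 symptoms with logit P = −0.4 ± s(t − 9)/4, six falling and six rising, 1 to 4 classes, 10 runs per cell, time uniform over 1 to 22 months. Entries are runs with two or more classes.

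| s (log-odds change per 4 months) | n = 500 | n = 1000 | n = 2000 |
|---|---|---|---|
| 0 | 0/10 | 0/10 | 0/10 |
| 0.25 | 0/10 | 0/10 | 9/10 |
| 0.5 | 10/10 | 10/10 | 10/10 |
| 1.0 | 10/10 | 10/10 | 10/10 |

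Where false classes arose, the mean gap between the highest and lowest class median of time since infection was 7.2 to 13.7 months, depending on the cell. With entry limited to 3 to 6 months, every run in every cell gave one class.

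**The case against.** The strongest reply is that a condensed article need not give analysis detail. The Subproject 3 entry in the aims textbox describes exploratory work, leaves the clustering criteria to be defined and allows for adjustments. The analysis section says that methods will be adapted to the questionnaire. The baseline form asks about the infection and its course, so time since infection is probably available, and an analysis plan not shown here could use it. This stands in part. A reader might infer that follow-up data are excluded from clustering, or that respondents will be pooled regardless of time. The text says neither: the data-source sentence does not say only. What remains is that both places that name a data source name the baseline form, and none connects the Step 4 data to the clusters.

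A second reply also has force. The effect requires symptoms recorded as they are when the form is answered. The questionnaire is not shown, and if it asks people to recall their whole course, profiles do not simply reflect stage.

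Third, every simulation input is assumed, including 1500 people with long COVID, and several plausible settings gave no false classes. Nor did the simulations test whether banding would lose true subtypes. These limits bear on the size of the effect and leave the mechanism intact.

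**Conclusion.** The concern holds in conditional form. The stated data source and open entry allow stages to be mistaken for types if symptoms are recorded as current and drift appreciably. The simulated range runs from no false clusters to false clusters in every run, and the article gives nothing that would place the study within it.

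Two stronger readings are tempting and unsupported. One is that the primary aim will be answered wrongly: this needs a drift and a time spread that the article does not report, and syndromic forms are one of several aims. The other is that care structures would be misdirected: the article names forms and care structures in the same aim but nowhere derives the second from the clusters. The point is a worthwhile, inexpensive improvement to an exploratory analysis.

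**What to change.** Amend Characteristics of the Participants and Type of Data and Analyses Planned to say that:

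1. time since infection enters the cluster analysis, as a covariate of class membership or through a sensitivity analysis within time bands;
2. the distribution of time since infection is reported for each cluster;
3. Subproject 3 also uses the Step 4 symptom data to check whether participants stay in their cluster before it is described as a syndromic form.

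A membership covariate shows how closely a cluster follows time but does not by itself remove a stage cluster, so items 2 and 3 are needed alongside it. A cluster should not be required to appear in more than one band, since a genuine form may be confined to one period.

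The cost is analysis time and a few sentences. No new data collection should be needed, provided that the infection questions already yield a date. The drawbacks are smaller samples per band and a stability check that rests on those who answer follow-up, who may differ from those who do not.

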### Ethics Approval and Consent to Participate

The study is registered in the German clinical trial registry (DRKS00026007) and has been approved by the institutional review board of both Hannover Medical School (9948_BO_K_2021) and University Medical Center Göttingen (29/3/21). Data security management plan has also been approved by Hannover Medical School. Informed consent will be obtained from all study participants subsequently in each study step (questionnaires, clinical assessment and specimen collection, and qualitative study). Each participant receives written information on study procedures and data management over the web-based questionnaire format.

Study participation is voluntary, and participants have the right to withdraw consent at any time and without disclosure of reasons for withdrawal. A trained member of the study team is available for questions at enrollment and thereafter.

In the further steps of the study, participants will be informed about specimen and data collection, as well as the storage of samples in the Hannover Biobank for future research projects. Study participation is voluntary, and participants have the right to withdraw consent at any time and without disclosure of reasons for withdrawal. Furthermore, they will receive a written data security protocol. A trained member of the study team is available for questions at enrollment and thereafter. All collected data will be pseudonymized and stored on servers of Hanover Medical School or University Medical Center Göttingen. Publications will include anonymized data. Blood samples will be transferred to the Biobank of Hanover Medical School.

### Description of All Processes, Interventions, Comparisons

The details of the study design are illustrated in Figure 1.

**Figure 1 figure1:**
[figure not shown]
Flow chart of DEFEAT Corona (Defense Against COVID-19 Study). ENT: ears, nose, and throat; OCT: optical coherence tomography.

#### Step 1: Baseline Questionnaire

The baseline questionnaire will include sociodemographic questions, questions about a SARS-CoV-2 infection, the process of the disease, possible late symptoms, and vaccination status. According to the participants’ answers in the basic questionnaire, they will be assigned into 3 groups: “No COVID,” “Ex-COVID,” and “Long COVID.” Questionnaire items were adapted from the World Health Organization Case Report Form [10] and the UK Long COVID guideline [11]. We also assessed quality of life (EQ-5D [12]) and social participation (IMET [13]; Multimedia Appendix 1).

The data of the baseline questionnaire will also be used in the cluster analysis to characterize the typical symptom complexes experienced by participants with long COVID.

#### Step 2: Obtaining Additional Clinical Characteristics in Ex-COVID and Long COVID Groups

A portion of the “Long COVID,” “Ex-COVID,” and “No COVID” groups will be invited for a personal clinical assessment to the outpatient clinic of Hanover Medical School. The clinical assessment will include blood sampling of 20-30 ml (eg, full blood count, electrolytes, liver enzymes, retention parameters, and SARS-CoV-2 antibodies), an ears, nose, and throat examination, optical coherence tomography angiography imaging, and a standardized medical examination by a trained physician. Some patients with long COVID will be invited to an additional web-based consultation.

#### Step 3: Qualitative Study of the Long COVID Illness Experience

According to the sociodemographic data gathered in the baseline questionnaire, a diverse group of participants with long COVID will be invited to participate in the qualitative arm of the study. We aim to perform 20-30 individual interviews and 10-20 focus groups to gain a deeper understanding about how people with various long COVID symptoms experience their illness, and how they perceive the illnesses impact on social participation. This includes relationships and activities among friends and family, education, profession, everyday life, health system, and leisure activities.

#### Step 4: Individualized, Modular, Follow-up Questionnaires

All participants will get invitations for modular questionnaires, depending on their answer in the baseline questionnaire (eg, how their children experienced the pandemic, if the participants stated that they had children). The follow-up questionnaires will contain questions about new infections with SARS-CoV-2, changes in symptoms and recovery from symptoms, further vaccinations, quality of life (EQ-5D), and social participation (IMET) over a longer period. The project will be accompanied by a patient- and public-led advisory board.

### Type of Data and Analyses Planned

Data preparation will be performed in SPSS (IBM Corp), data analysis in R (version 4.1.1; The R Foundation), and visualizations with GraphPad Prism (GraphPad Software Inc) and R. Types of data are mainly ordinal or numerical and sometimes strings of a free text, depending on the questions. Optical coherence tomography images will be analyzed with MATLAB (MathWorks), and values will be created for vessel density and vessel distance. During the data preparation, data quality will be checked, and the handling of missing values will be addressed. Summary statistics and standard visualizations will be computed. Within the collected data, symptom clusters after an infection with SARS-CoV-2 will be found using machine learning methods. Established methods of cluster and symptom cluster analysis will be adapted and extended for the specific questionnaire. Logistic regression will be applied to identify specific risk factors for development of long COVID.

Semistructured interviews and focus groups will last about 45-75 minutes. Interview and focus group data will be recorded and transcribed according to the simplified rules of Kuckartz [14] and Dresing and Pehl [15] and subsequently analyzed using qualitative content analysis according to Mayring [16] and Kuckartz [14].

Our mixed-methods approach to exploring social participation includes data from standardized questionnaires and qualitative interviews and focus groups. These data will be combined or triangulated to gain a deeper understanding of the social participation and the illness experience of persons experiencing long COVID symptoms.

